#### 2.8.1. Primary Outcome

The efficacy of the intervention in relation to the suspension of BF at 6 months will be assessed from two-input tables with application of the chi-square test (χ^2^). Likewise, multivariate logistic regression analysis will be used, with calculation of the odds ratio (OR) corresponding to the suspension of BF at 6 months, and the 95% confidence interval (95%CI).

#### 2.8.2. Secondary Outcome

The level of HL (adequate vs. inadequate) with the HLS-EU-Q16 screening tool and the characteristics of the women who gave up BF at 6 months (yes/no) will be assessed via two-input tables with application of the chi-square test (χ^2^) for qualitative variables. Multivariate logistic models will be used in order to analyze the magnitude of the association with BF at 6 months. The adjusted odds ratio (OR) and 95% confidence interval (95%CI) will be calculated, and *p*-values will be presented.

Data analysis will be performed using SPSS v.26.0 for Windows (IBM Corp. 2018, Armonk, NY, USA) and R (R project 2019, version 4.0.2). The level of statistical significance defined was *p* < 0.005.

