## Abstract

Purpose: The primary aim of this study is to determine the influence of an intervention in women based on a free mobile application (LactApp^®^, Barcelona, Spain) in maintaining breastfeeding (BF) up to 6 months postpartum. The secondary aim is to assess the effect of health literacy (HL) on breastfeeding duration. Methods: A multicenter, randomized controlled clinical trial of parallel groups will be carried out. Women will be randomly assigned to each of the parallel groups. In the control group, usual clinical practice will be followed from the third trimester of pregnancy to promote BF. In the intervention group, and in addition to usual clinical practice, the women will use a free mobile application (LactApp^®^) from the third trimester to 6 months postpartum. The type of BF at birth, at 15 days and at 3 and 6 months postpartum and the causes of cessation of BF in both groups will be monitored. The hypothesis will be tested using inferential analysis, considering an alpha of 5%. The study protocol was approved by the Clinical Research Ethics Committee of Hospital de la Ribera (Alzira, Valencia, Spain) in February 2021. A per protocol analysis and an intention-to-treat analysis will be performed. Discussion: This study will identify the influence of a mobile application on improving BF rates. If the application proves effective, we will have a tool with free information available to any user at any time of day, which may be complemented by normal clinical practice and be integrated into our health care system. Trial registration: ClinicalTrials.gov ID: NCT05432700.

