At present there are new interventions that still need to be tested for their long-term efficacy, such as the use of mobile applications [15,16]. In this context, mobile health services, mHealth, are defined as medical and public health practices compatible with mobile devices such as smartphones, patient monitoring devices, personal digital assistants and other wireless devices [17,18]. A large proportion of the European population consults online information for its health problems [19]. These users consider that the information they find is going to be useful for them [20]. On the other hand, healthcare systems increasingly make use of online services in support of users and healthcare professionals, including the utilization of mobile applications [21]. Nevertheless, it must be taken into account that the use of such tools is not proportional within the population, and that we must ensure that the information provided is not only based on the best available scientific evidence, but is also accessible to women at risk of social exclusion [22]. In line with different studies, the application of a protocolized intervention that is accessible and adapted to the needs of women effectively improves the rates and duration of BF [4,13,14,23,24,25,26].

On the other hand, while there is no single definition of health literacy (HL), the term refers to user knowledge and skills in adequate decision making in sociosanitary care [27]. Such skills include reading, writing, making calculations, communication capacity and—increasingly so—the use of information technologies. Deficient HL has been related to poor health outcomes, including the early suspension of BF [28,29,30], which is one of the most relevant public health problems and is of special importance in the maternal–childhood population.

In Spain, few randomized clinical trials have analyzed the benefits of interventions based on mobile devices in BF. The main objective of this study is to determine the influence of an intervention program in maintaining BF up to 6 months postpartum. The secondary aim is to assess the HL level of the participants and its association to the early (less than 6 months postpartum) suspension of BF.

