### 2.2. Recruitment

The study will be conducted in three public hospitals in eastern Spain (Hospital Lluis Alcanyis, Hospital General de Castellón, and Hospital Universitario de la Ribera), and in one hospital in the western part of the country (Hospital San Pedro de Alcántara de Cáceres). The four hospitals serve a total population of 500,000 inhabitants, with an average of 5000 births a year. The women will be included during the third trimester of pregnancy in the different primary care midwife consulting rooms of each of the participating centers.

The study exclusion criteria are: females under 16 years of age; women with cognitive impairments, language barriers, or illiteracy (not able to read Spanish); non-availability of a mobile device with internet connection; newborn infants with congenital malformations; twin or multiple pregnancies; and admission to the Neonatal Intensive Care Unit (NICU), prenatal death or stillbirth, or postpartum complications requiring admission of the mother to the intensive care unit (ICU). Women failing to respond to the automated messages from the platform after three attempts will also be excluded, in the same way as those women in the control group who have used the LactApp^®^ application on their own initiative. Figure 1 shows the monitoring to be carried out during the study.

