### 2.4. Sample Size Determination

Based on previous studies [15], and assuming the BF suspension rate at 6 months to be 60% in the control group versus 40% in the intervention group, with a significance level of *p* < 0.05 and a statistical power of 85%, a balanced design would require 333 women in total. Compensating for an estimated loss rate of 20%, the estimated final total sample size would be 399 women.

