### 2.7. Baseline Variables

The following variables will be collected at baseline:

- Sociodemographic variables: maternal age at the probable date of delivery, country of origin (Spain/foreign), level of education (primary school or lower/secondary school/university), employment status (self-employment/professional/managerial employment/employee/unemployed/student/not looking for a job), civil status (single/married/separated-divorced), partner (yes/no), number of live offspring, previous experience with breastfeeding (yes/no), participation in maternal education groups (yes/no), reception of previous information on BF (yes/no), and participation in BF support groups (yes/no).

- Variables related to health literacy: as a screening tool, use will be made of the HLS-EU-Q16, which evaluates the HL of the population based on 16 items scored by means of a Likert scale from “very easy” to “very difficult”. This is a unifactorial scale with good internal consistency as measured by McDonald’s omega, with a value of 0.982 in the Spanish population [34].

- Variables referred to health-related quality of life: use will be made of the EQ-5D [40] in the baseline measurements and at 3 and 6 months. This scale is very sensitive to quality of life measures and has been shown to be even more sensitive in women [41]. It comprises 5 items related to mobility, personal care, daily activities, pain/discomfort, and anxiety/depression. It uses a visual analogue scale (VAS) from 0 to 100 for measuring health condition at the time of application of the questionnaire [42].

- Variables related to self-efficacy of BF: the measurement of self-efficacy will be made with the BSES-SF scale in its Spanish version [37]. This instrument consists of 14 items scored by means of a Likert scale from 1 (not at all) to 5 (always). The BSES-SF is a unidimensional scale with a Cronbach alpha of 0.79 in its Spanish version.

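### Section 2.8.2 uses the 16-item health literacy score only as adequate versus inadequate; if the association is graded, this costs precision on the trial's one secondary aim

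*Protocol article*

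**What the plan says.** The protocol article states one secondary aim. The abstract words it as "The secondary aim is to assess the effect of health literacy (HL) on breastfeeding duration". The introduction, quoted here up to its last word, puts it as "The secondary aim is to assess the HL level of the participants and its association to the early (less than 6 months postpartum) suspension of". Both concern the association between health literacy and breastfeeding.

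Section 2.7 describes the instrument as one that "evaluates the HL of the population based on 16 items scored by means of a Likert scale", and adds: "This is a unifactorial scale with good internal consistency as measured by McDonald’s omega". On the protocol's own account, then, a single total score is meaningful, and the items needed to form it are collected at baseline.

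Section 2.8.2 uses the instrument in two levels: "The level of HL (adequate vs. inadequate) with the HLS-EU-Q16 screening tool", cross-tabulated against giving up breastfeeding at 6 months and tested by chi-square. It continues: "Multivariate logistic models will be used in order to analyze the magnitude of the association with BF at 6 months". That sentence does not say how health literacy enters the model. No model using the total score is described, and no reason is given for the split.

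**The concern.** A two-level variable treats every woman on one side of the cut as having the same health literacy, whether she sits just beside the cut or at the end of the scale. If the chance of stopping breastfeeding changes gradually along the scale, that difference within groups carries information, and the split discards it.

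The only sample-size calculation (section 2.4) is for the comparison of the two arms. The health literacy aim has no precision target of its own, which is ordinary for an observational secondary aim. It does mean that any lost information goes straight into a wider confidence interval and lower power for that aim.

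**Working it through.** **The plan's own figure.** There is none for the health literacy analysis. The 333 women in section 2.4 are used below only as an assumed number with a known outcome. Whether 333 follows from its stated inputs is a separate question, and the percentage losses do not depend on it.

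**Inputs from the protocol.** Two-level exposure (2.8.2); 16 items forming one factor (2.7); 333 women (2.4); and suspension rates from section 2.4, "assuming the BF suspension rate at 6 months to be 60% in the control group versus 40% in the intervention group", which with equal arms average (60% + 40%)/2 = 50%.

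**Assumed inputs, because the protocol gives none.** Shape of the score, a total running from 0 to 16, position of the cut-off, share of women below it, and size and shape of the association.

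**Step 1: normal score, linear log-odds effect.** The information kept by a cut that puts a share q in the low group is φ(z_q)² / [q(1 − q)].

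| Split | Kept | Lost | 333 women act like |
|---|---|---|---|
| 50/50 | 0.637 | 36% | 333 × 0.637 = 212 |
| 30/70 | 0.576 | 42% | 333 × 0.576 = 192 |
| 20/80 | 0.490 | 51% | 333 × 0.490 = 163 |

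**Step 2: bounded or skewed scores.** With a linear effect, the information kept is the squared correlation between score and split, cov² / [variance × q(1 − q)].

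A flat 0–16 score has mean 8 and variance (17² − 1)/12 = 24. Cutting below 9 gives q = 9/17 and a low-group mean of 4, so:
- cov = (9/17) × (4 − 8) = −2.118, and cov² = 4.484;
- q(1 − q) = 72/289 = 0.249;
- kept = 4.484 / (24 × 0.249) = 0.75, so the loss is 25%.

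Beta-binomial shapes on 0–16, as examples (share in the low group in brackets):

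| Mean, SD | Cut below 9 | Cut below 11 | Cut below 13 |
|---|---|---|---|
| 11.4, 4.9 | 23% (0.27) | 22% (0.35) | 29% (0.45) |
| 12.3, 3.1 | 45% (0.13) | 32% (0.26) | 33% (0.44) |
| 12.8, 2.5 | 63% (0.06) | 40% (0.17) | 32% (0.39) |

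Over all shapes tried, most losses lay between about 20% and 60%. The extremes were 19% and 73%, the latter with only 3% of women below the cut.

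**Step 3: power if the effect is graded.** 2,000 simulated trials per setting, 333 women, 50% suspension overall, normal score, log odds ratio 0.30 per SD (odds ratio e^0.30 = 1.35), two-sided 0.05, no covariates.

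| Split | Score | Two levels |
|---|---|---|
| 50/50 | 77% | 58% |
| 30/70 | 76% | 53% |
| 20/80 | 76% | 47% |

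**Step 4: power if risk steps exactly at the cut.** Same settings, with suspension 58% below the cut and 42% above.

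| Split | Score | Two levels |
|---|---|---|
| 50/50 | 64% | 82% |
| 30/70 | 54% | 77% |

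The order reverses. The sign of the difference depends on the shape of the association, which the protocol does not give.

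Steps 3 and 4 use 0.05, as in the abstract and section 2.4; section 2.8.2 states 0.005. That discrepancy changes the power figures but not the percentage losses in steps 1 and 2.

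**The case against.** The strongest case for the plan has four parts.

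*The split has a purpose.* The protocol calls the questionnaire a screening tool, and its limitations section treats women with limited health literacy as a group of interest. An odds ratio for inadequate versus adequate literacy answers that interest directly. This stands as a reason to report the categories. It does not make them the best sole form of the exposure.

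*Risk may step at the cut-off.* Then the split is the better analysis, as step 4 shows. This stands as a possibility. The introduction and limitations link poor literacy to worse outcomes and decisions, which gives a direction but no threshold.

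*The coding in the logistic model is not fixed.* The two-level wording is attached to the tables and the chi-square test, and the model could in principle carry the score. This stands as a caveat, but no score-based model is described. Section 2.8 does plan Mann–Whitney comparisons of means in a sentence on homogeneity of groups that also mentions suspension at 6 months. That sentence is ambiguous, and it would supply a test without an adjusted estimate of the association.

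*The size is not known.* This stands in full. A reader might infer that the split must waste at least a third of the information. That holds for a normal score with a linear effect, but several bounded shapes in step 2 lose less. A reader might also infer, from the exclusion of women who cannot read Spanish, that the low-literacy group will be small and the loss therefore large. Being able to read is not the same as scoring adequate on this questionnaire, and the protocol gives no expected share, so that inference should not be drawn.

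**Conclusion.** The point holds in conditional form. Section 2.8.2 specifies health literacy only in two levels for the one secondary aim, while a usable score is collected. If the association is graded, the loss is 36% at a 50/50 split and 51% at 20/80 under a normal score and linear log-odds, and roughly 20% to 60% for bounded or skewed scores. If there is a true threshold at the cut-off, nothing is lost.

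The score shapes, splits and effect sizes are assumptions, so the power figures illustrate the mechanism and do not predict this trial. Nor do the documents support saying in advance that a null health literacy result would be due to the cut. The split does not touch the primary comparison and contradicts nothing else in the protocol. This is a cheap improvement in precision, not an error that threatens the trial's main conclusion.

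**What to change.** In section 2.8.2, add a sentence that prespecifies the HLS-EU-Q16 total score as a continuous term in the logistic model for suspension at 6 months, with the odds ratio per SD or per point. Check linearity with a quadratic or spline term, and keep the adequate/inadequate comparison alongside. State before the data are analysed which of the two estimates carries the secondary aim, so that the coding is not chosen from the results.

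The cost is one sentence and no new data. There are two downsides. An odds ratio per point is less familiar to clinicians than a two-group contrast, and the score is the less powerful form if the effect is a true threshold. Retaining the categories and checking linearity limits both.

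### The analysis section sets significance at p < 0.005, but the abstract and sample size use 5%, so the decision rule is contradictory and the stated 85% power does not hold

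*Protocol article*

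**What the plan says.** The protocol article gives the significance level in three places.

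- Abstract: "The hypothesis will be tested using inferential analysis, considering an alpha of 5" per cent.
- Section 2.4, Sample Size Determination: "with a significance level of *p* < 0.05 and a statistical power of 85" per cent. The assumed rates are "assuming the BF suspension rate at 6 months to be 60% in the control group versus 40% in the intervention group". From these the protocol states that "a balanced design would require 333 women in total", and then "Compensating for an estimated loss rate of 20%, the estimated final total sample size would be 399 women".
- Section 2.8.2, Secondary Outcome, after the sentence naming the software: "The level of statistical significance defined was *p* < 0.005".

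Section 2.8.1, Primary Outcome, specifies a chi-square test and a logistic regression odds ratio with a 95% confidence interval, but no significance level. Section 2.8.2 also uses 95% intervals. The article mentions no multiplicity adjustment and gives no other reason for a level of 0.005.

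**The concern.** The significance level decides whether the trial is declared positive, and the document gives two values a factor of ten apart. The stricter one stands in the analysis section, which is where an analyst would look for the rule.

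Three things follow:

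- The same data can support opposite conclusions, depending on which part of the protocol is followed. If this is left until results are known, the choice is made with the data in hand.
- The power claimed in section 2.4 refers to a test at 0.05. It does not carry over to a test at 0.005.
- For a p-value between 0.005 and 0.05, the planned 95% interval for the odds ratio would normally exclude 1 while the stated rule calls the result non-significant.

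**Working it through.** **Inputs.** From section 2.4: suspension rates p1 = 0.60 and p2 = 0.40, equal arms, 333 women before losses, 399 recruited, 20% loss, power 85%. Alpha is 0.05 (abstract, section 2.4) or 0.005 (section 2.8.2). Sidedness is not stated. I assume two-sided, which fits a chi-square test and 95% intervals. Evaluable women after losses: 399 × 0.80 = 319.2, about 159.5 per arm.

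**Sample size formula (pooled variance under the null).** With mean rate 0.50:

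n per arm = [z(1−α/2) × √(2 × 0.50 × 0.50) + z(power) × √(0.60 × 0.40 + 0.40 × 0.60)]² / 0.20²

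**The plan's own figure.** At α = 0.05 and 85% power:

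(1.960 × 0.7071 + 1.036 × 0.6928)² / 0.04 = 110.7, so 111 per arm, 222 in total (242 with continuity correction).

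The stated 333 is not reproduced.

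**Size needed at 0.005.** With 2.807 in place of 1.960:

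(2.807 × 0.7071 + 1.036 × 0.6928)² / 0.04 = 182.6, so 183 per arm, 366 evaluable (386 with continuity correction).

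Allowing for 20% losses, 366 / 0.80 = 457.5, so 458 recruited.

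**Power.** Power = Φ[(0.20 − z(1−α/2) × √(0.50/n)) / √(0.48/n)], n per arm.

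| Evaluable women | n per arm | Power at 0.05 | Power at 0.005 |
|---|---|---|---|
| 333 | 166.5 | 95.8% | 80.5% |
| 319 | 159.5 | 95.0% | 78.3% |

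For example, 333 women at 0.005: (0.20 − 2.807 × 0.0548) / 0.0537 = 0.86, and Φ(0.86) = 0.805. With continuity correction the 0.005 column becomes 77.3% and 74.8%.

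**Where the conclusion flips.** With 319 evaluable women and a pooled rate near 0.50, the standard error is √(0.25 × 2/159.5) = 0.0560.

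- Critical difference at 0.05: 1.960 × 0.0560 = 0.110.
- Critical difference at 0.005: 2.807 × 0.0560 = 0.157.

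Observed differences between 11.0 and 15.7 points are positive under the abstract and section 2.4 and negative under section 2.8.2. If the true difference is the planned 20 points, the chance of landing in this band is 95.0% − 78.3% = 16.7%. If it is 15 points (57.5% versus 42.5%), the same formula gives about 32%.

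**The case against.** The strongest reply is that this is a typing slip. The abstract, section 2.4 and every planned confidence interval fit 5%, and a single extra zero does not. That is the likeliest explanation. It does not remove the problem, because the wrong value would stand in the text that governs the analysis, and nothing in the article confirms which value was intended.

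Four further points deserve a fair hearing.

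- **Scope.** The sentence stands under the secondary outcome heading, and the abstract ties 5% to the hypothesis. One could read 0.005 as applying to secondary analyses only. However, it follows a general statement about software and is the only level in section 2.8, so the general reading is the natural one. The text should not leave this open.
- **Power.** The loss at 0.005 is moderate: 4.5 to 6.7 points below 85%. This is correct, and the ambiguous decision rule matters more.
- **Sample size.** The 85% is not the two-sided power at 0.05 either, since 333 women give 95.8%. This is a separate defect in section 2.4, and correcting the threshold will not cure it.
- **Sidedness.** It is unstated, and the null hypothesis in the Discussion is worded directionally. A one-sided test at 0.005 needs 324 women for 85% power, fairly close to 333, but the protocol nowhere describes such a test.

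Reporting 95% intervals beside a stricter threshold is not an error in itself; here it is mainly evidence that 5% was intended.

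**Conclusion.** The concern holds. The protocol states two incompatible significance levels, 0.05 and 0.005, without explanation, and the stricter one reads as governing the primary test. With about 319 evaluable women, the trial's conclusion depends on which is used whenever the observed difference lies between about 11.0 and 15.7 points. At 0.005 the power is about 78% to 81%, not 85%, and 366 evaluable women would be needed to restore it.

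The figures assume 60% versus 40%, equal arms, a two-sided test without continuity correction and losses of exactly 20%. The contradiction itself needs none of these assumptions. It must be corrected because it concerns the primary decision threshold, even if its origin is a slip.

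**What to change.** In section 2.8.2, replace 0.005 with a two-sided significance level of 0.05, and say that it applies to the primary test in section 2.8.1. This agrees with the abstract, section 2.4 and the 95% intervals; the word two-sided is an addition, since sidedness is not stated at present. Make and date the correction before any comparison of outcomes by group.

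If 0.005 was intended, say so and why, change the abstract and section 2.4 to match, restate the power as about 78% with 319 evaluable women (or plan for 366 evaluable, 458 recruited, to keep 85%), and report 99.5% confidence intervals.

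The first option is a one-line change and needs no extra women or data. While section 2.4 is open, its arithmetic should be checked too: 333 does not follow from 0.05 and 85% power, and 399 is about 333 × 1.2 = 399.6, whereas allowing for a 20% loss gives 333 / 0.80 = 416.25, so 417.
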